### Recruitment

In this study, participants will be recruited through two pathways. First, through the assistance of nurse managers of relevant departments in hospitals has been established to recruit, post or place leaflets, posters in departments of hospitals, and have researchers promote the project after the daily treatment of patients to attract interested patients. Secondly, through network: Release and diffuse recruitment information through WeChat friend circle, WeChat group, Weibo and other network platforms.

### Assignment of intervention

Before randomization grouping, the children's medical records will be read carefully to obtain information about their demographics and diseases. Patients will be numbered according to the enrollment order and assigned to the experimental and control groups according to the random number table method. Statistical analyses will be performed to compare the balance of the two groups in terms of age, sex, ALT, BMI, and quality of life scores. The child's parents are entered into the same group as the child.

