### Sample size

Sample size estimation will be performed using Professional Association for SQL Server (PASS) 2014 software for grasp degree analysis (Power Analysis). The mean effect size of the lifestyle intervention on the improvement of ALT indicators (Effect size) was estimated to be −1.35 according to the Meta-analysis of the clinical study conducted by Utz-Melere et al. (14, 15). The sample size required will be 32 study subjects per group by power analysis in reaching 80% effectiveness, using a two-tailed test with a test level of 0.05. Based on a 20% failure rate, this part of the study required 80 subjects, 40 in each group.

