### Statistical analyses

First, after eliminating the questionnaires that did not meet the requirements, all data will be organized and quantified and then entered the statistical software in pairs for analysis. Then statistical description of the data will be done, including descriptive statistical analysis of patients' general information, the mean and standard deviation will be used to describe the measurement data that conformed to normal distribution. Finally, statistical inferences will be made and *t*-test, ANOVA. The effect of the intervention on NAFLD w analyzed using McNemar's test for paired categorical data and χ^2^ or Fisher's exact test for independent categorical data, as appropriate. Changes in continuous variables will be analyzed using paired Student *t*-test. Statistical significance will be set at *P* < 0.05. Using analysis of covariance we evaluated whether baseline variables predicted changes in liver fat content and ALT during 6 months of treatment.

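### ALT balance between arms is checked at baseline, but no comparison of the arms adjusted for baseline ALT is stated

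*Protocol article*

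**What the plan says.** All references are to the protocol article.

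- **Assignment of intervention.** Children are numbered as they enrol and "assigned to the experimental and control groups according to the random number table method". Then: "Statistical analyses will be performed to compare the balance of the two groups in terms of age, sex, ALT, BMI". The list also includes quality of life. No test, threshold or consequence of the result is given.
- **Outcome.** ALT and GGT are the primary outcomes, measured at baseline and at five later visits up to week 48.
- **Statistical analyses.** The methods named for continuous data are the t-test and ANOVA, with paired t-tests for changes. "Statistical significance will be set at *P* < 0.05". ANCOVA appears once, to ask whether baseline variables predict 6-month change in liver fat and ALT. It is not described as the comparison of the two arms.
- **Sample size.** "The sample size required will be 32 study subjects per group by power analysis in reaching 80% effectiveness". The test is two-sided at 0.05. After a 20% allowance for losses, "this part of the study required 80 subjects, 40 in each group".

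**The concern.** In a randomised trial, any baseline difference between arms is due to chance, so a significance test of that difference answers a question already settled. What matters is whether the realised difference is large enough, in a variable prognostic enough, to move the treatment comparison. A P value does not measure that, and in a small trial a non-significant result leaves room for a sizeable difference.

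This would matter little if the arms were compared with adjustment for baseline ALT. As written, they are not: an ALT difference that passes the check goes straight into a t-test or ANOVA. At stake are the credibility of the one result obtained if the arms start unequal, and the precision lost by leaving out a strong predictor that is measured anyway.

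**Working it through.** **Inputs from the article.** 40 per arm randomised; 32 per arm evaluable; two-sided 0.05; 80% power; effect size 1.35 in absolute value, read as a standardised mean difference because no unit is given.

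**Assumed.** The correlation r between baseline and follow-up ALT is not in the article; r = 0.5–0.7 is used, with 0.3–0.8 as a wider range. SDs are taken as equal at baseline and follow-up, with approximate normality.

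**1. The plan's own figures.** The allowance for losses reproduces: 32/(1 − 0.20) = 40 per arm, 80 in all. The 32 does not follow from 1.35, which needs 10 per arm by t-test at 80% power; 32 per arm corresponds to about 0.71 SD. That is a separate matter, used here only to give two effect sizes for scale.

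**2. What a balance test passes.** The SE of a standardised baseline difference is √(2/40) = 0.2236. The largest non-significant difference is t(0.975, 78) × 0.2236 = 1.991 × 0.2236 = **0.445 SD**. With 32 per arm it is 0.50 SD.

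**3. How often this arises at 40 per arm** (normal theory).
- |difference| ≥ 0.3 SD: 18% of trials; about 13% reach 0.3 SD and still pass.
- |difference| ≥ 0.4 SD: 7.4%; about 7.4 − 4.7 = 2.7% reach 0.4 SD and still pass.

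**4. Effect on an unadjusted comparison of follow-up ALT, given an imbalance of 0.4 SD and no treatment effect.** The expected difference is r × 0.4 and its SD is √(1 − r²) × 0.2236. The test rejects beyond 1.96 × 0.2236 = 0.438.

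| r | Expected shift (SD) | SD of the difference | Type I error |
|---|---|---|---|
| 0.5 | 0.20 | 0.194 | 11.0% |
| 0.6 | 0.24 | 0.179 | 13.4% |
| 0.7 | 0.28 | 0.160 | 16.1% |

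Using the t limit of 0.445 with the same normal tails gives 10.3%, 12.6% and 15.0%. Simulating the t-test with the imbalance held at 0.4 SD gives 10.8% at r = 0.5 and 15.8% at r = 0.7. Hence about 11–16%.

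At the 0.445 SD limit the shift is 0.13–0.36 SD for r = 0.3–0.8. That is 10–26% of 1.35, or 19–50% of 0.71.

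**5. If change from baseline is compared instead.** The shift is (1 − r) × imbalance in the opposite direction. At 0.4 SD that is 0.20 SD (r = 0.5) or 0.12 SD (r = 0.7), with type I error about 11% and 9%.

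**6. Over all randomisations.** Simulation of 40,000 trials at 40 per arm gives 4.7–5.1% for the unadjusted tests. Among trials that pass the balance test it is 3.5–4.4%.

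**7. What adjustment changes.** Under a linear model, ANCOVA removes the imbalance term and multiplies the variance of follow-up values by 1 − r². The effect in residual SD units is therefore 0.71/√(1 − r²). Power at 32 per arm:

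| r | 1 − r² | Unadjusted follow-up | ANCOVA |
|---|---|---|---|
| 0.3 | 0.91 | 80% | 83% |
| 0.5 | 0.75 | 80% | 90% |
| 0.7 | 0.51 | 80% | 97% |
| 0.8 | 0.36 | 80% | 99.7% |

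Against change scores, whose variance factor is 2(1 − r), the gain is smaller: the ratio is (1 + r)/2, or 0.75 at r = 0.5 and 0.85 at r = 0.7.

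**The case against.** **The design is valid without adjustment.** This is correct. Across randomisations the unadjusted test is unbiased and holds its level, and among trials that pass the check it is slightly conservative. A reader might infer that the trial's error rate is inflated to 11–16%; it is not. Those figures apply once an imbalance of 0.4 SD has occurred, which is uncommon. The conditional view is still relevant, because a balance check is itself an attempt to judge the allocation actually obtained.

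**The effect may be too large for this to matter.** Against 1.35 SD, the worst imbalance that passes shifts the result by about a quarter and would not reverse it. Power at 32 per arm is then already 99.96%. The argument has more force if the effect is nearer 0.71 SD.

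**Significance tests are not named.** True; the text speaks only of statistical analyses, and no action is tied to their result. The reading rests on P < 0.05 being the only criterion given. It is also unclear whether the t-test is on follow-up values or changes, so both are shown above.

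**A reader might infer that the allocation itself is defective**: unstratified, unable to give 40 per arm, and made worse by recruiting through two pathways. The article does not support this. It is a condensed account that is silent on blocks and strata, and a random number table can be used so as to give equal arms. Leaving 80 children at one hospital unstratified is a legitimate choice, and nothing shows that recruitment pathway is prognostic.

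**Conclusion.** The point holds as a weakness of the stated analysis, not of the randomisation. The article plans a look at baseline ALT that cannot establish comparability at this size, and states no baseline-adjusted comparison of arms on ALT. Validity over repeated randomisations is intact. What is lost is protection against the imbalance that actually occurs, together with precision that is available at almost no cost.

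The 0.445 SD limit follows from the article's own sample size, taking 0.05 as the test level. The 11–16% and the power gains rest on an assumed correlation. All figures on the SD scale are approximate, because entry requires a persistently raised ALT, so baseline values are truncated below and probably skewed. Removing the balance tests without adjusting would change no result; adjustment is the part that matters.

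**What to change.** 1. **Statistical analyses.** State that the primary between-arm comparison of ALT is an ANCOVA, or a longitudinal model over the planned visits, with baseline ALT as a continuous covariate, probably on the log scale, whatever balance is observed. Do the same for GGT with its own baseline. If the log scale is used, say that the effect will be reported as a ratio.
2. **Assignment of intervention.** Replace the balance analyses with a descriptive table of baseline values by arm, and state that no balance test decides the analysis.

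The cost is a short amendment and one covariate per model. Baseline ALT is already needed for eligibility and GGT is measured at baseline, so no new data are required. The change can be made after enrolment has started, provided it is fixed before outcome data are examined by arm. Blocking, or stratifying by ALT, remains optional; if either is used, the article should say so, but the correction does not depend on it.

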### Blinding

Study personnel involved in the data assessment of the study are blinded to the patients' treatment assignment. The clinical doctors that deliver the study treatment are not blinded and are therefore uninvolved in the patients' data assessments related to this study. Data analysts are blinded to group allocation.

### Data collection and management

First, members of the research team explained the purpose and significance of the study to the participants and obtained consent and support. Then, subjects who met the inclusion criteria were selected and the purpose, content, and significance of the survey were explained to them, explaining that the study results would be used only for scientific research and that medical confidentiality would be strictly observed. After that, the investigator personally distributed the questionnaire, and the patients filled it out under a uniform instructional language. For patients with no reading ability or writing difficulty but could understand and answer the questions correctly, the researcher will repeat the questions and options in a neutral tone, and the patients themselves chose. The researcher assisted in filling out the questionnaire, which will be distributed and collected on the spot. The questionnaires took about 25–30 min to fill out; finally, the researcher carefully check the collected questionnaires and promptly eliminated invalid ones. In addition, anthropometric measurements [length, weight, waist circumference (waist circumference) and blood pressure], blood sampling [serum alanine aminotransferase (ALT), insulin, glucose and lipids] and 1H-MRS were taken to determine hepatic steatosis. Use the collected height and weight data to calculate age-adjusted BMI-z scores (16).

### Statistical analyses

First, after eliminating the questionnaires that did not meet the requirements, all data will be organized and quantified and then entered the statistical software in pairs for analysis. Then statistical description of the data will be done, including descriptive statistical analysis of patients' general information, the mean and standard deviation will be used to describe the measurement data that conformed to normal distribution. Finally, statistical inferences will be made and *t*-test, ANOVA. The effect of the intervention on NAFLD w analyzed using McNemar's test for paired categorical data and χ^2^ or Fisher's exact test for independent categorical data, as appropriate. Changes in continuous variables will be analyzed using paired Student *t*-test. Statistical significance will be set at *P* < 0.05. Using analysis of covariance we evaluated whether baseline variables predicted changes in liver fat content and ALT during 6 months of treatment.

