There are also some limitations that need to be addressed. Firstly, we estimate that there will be an attrition rate of ~10% of children who enroll in the study, mostly due to financial issues or time constraints. To minimize the effect of the biases, we will conduct the analysis on an intention-to-treat basis. It is important to consider that although this study will be conducted in the hepatobiliary ward of a specialist women's and children's hospital in Shaoxing, Zhejiang Province, this may lead to limitations in the findings. However, we are conducting a formative evaluation throughout the implementation of the project to explore which interventions or environmental factors may hinder or contribute to the effectiveness of this project at different stages of implementation to facilitate global replication.

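### Intention-to-treat is promised as the remedy for attrition bias, but discarding returned questionnaires and using paired tests for change do not deliver it

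*Protocol article*

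**What the plan says.** The Discussion of the protocol article expects some loss of enrolled children ("we estimate that there will be an attrition rate of ~10% of children who enroll in the study") and gives one remedy: "To minimize the effect of the biases, we will conduct the analysis on an intention-to-treat basis".

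The methods sections describe the handling of data differently:

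- Data collection and management, on questionnaires: "the researcher carefully check the collected questionnaires and promptly eliminated invalid ones". The article does not say what makes a form invalid.
- Statistical analyses, as the first step: "after eliminating the questionnaires that did not meet the requirements, all data will be organized and quantified". The requirements are not given.
- Statistical analyses, on continuous change: "Changes in continuous variables will be analyzed using paired Student" t-test. The effect on NAFLD as a paired category is "analyzed using McNemar's test for paired categorical data". A t-test, ANOVA, chi-square or Fisher's exact test, and an analysis of covariance for baseline predictors of change are also named.

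The Outcome section makes serum markers (ALT and GGT) primary and lists quality of life as secondary. All outcomes are measured at baseline and at weeks 4, 16, 24, 36 and 48. Sample size allows for loss: "Based on a 20% failure rate, this part of the study required 80 subjects". The Blinding section says that data assessors and analysts do not know the allocation.

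**The concern.** Intention-to-treat sets which children are analysed and in which arm. It does not supply an outcome for a child who has none, and it does not fit with deleting outcome data already collected on grounds left to judgement. Two separate gaps follow.

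The first concerns questionnaire outcomes. An undefined validity rule applied at follow-up selects data after randomisation. If form quality depends on arm or on how the child is doing, the comparison of quality of life is no longer protected by randomisation.

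The second concerns ALT and GGT. A test on pairs needs both members of the pair. Without imputation, a child who lacks the chosen follow-up value leaves the analysis, and the bias that the Discussion wants to limit comes back.

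Unequal loss is plausible here. Table 2 asks intervention families for daily uploads and for home visits about every two weeks. Control families have education at hospital visits and a monthly review. The Discussion itself names time constraints as a main reason for leaving. A report from this plan could be labelled intention-to-treat while the effective analysis set is smaller and selected.

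**Working it through.** **1. Which data each rule reaches**

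| Rule | Quality of life, other questionnaires | ALT, GGT |
|---|---|---|
| Removal of invalid questionnaires | Yes; after randomisation at the five follow-up visits | No; these are blood tests |
| Paired t-test on change | Only pairs with both values | Only pairs with both values |
| McNemar's test | Paired categories only | Not applicable while continuous |

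The other named tests share the second limit. A t-test, ANOVA, chi-square or Fisher's test, or covariance analysis of change cannot use a child with no follow-up value unless one is imputed. The section mentions neither imputation nor intention-to-treat. It also does not say that dropouts are excluded.

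**2. The plan's allowance for loss**

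Inputs from Sample size: 32 evaluable per arm and 20% loss. 32 / (1 − 0.20) = 40 per arm, 80 in total. This reproduces the plan's figure.

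Children left out of 80 if loss is not recovered:

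- at 10%: 0.10 × 80 = 8 lost, 72 remain (36 per arm)
- at 20%: 0.20 × 80 = 16 lost, 64 remain (32 per arm)

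**3. Possible size of bias in a between-arm comparison**

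Assumptions, none of them in the documents: loss is informative in one arm only; dropouts in that arm are 0.5 to 1.0 SD worse than completers; loss in the other arm is unrelated to outcome; the true effect is zero; the comparison is an unpaired t-test at two-sided 0.05.

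Compared with the mean of everyone randomised to that arm, the completers' mean is off by

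bias = (proportion lost) × (difference between dropouts and completers).

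- 10% loss: 0.10 × 0.5 = 0.05 SD; 0.10 × 1.0 = 0.10 SD
- 20% loss: 0.20 × 0.5 = 0.10 SD; 0.20 × 1.0 = 0.20 SD

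The standard error of the difference in SD units is √(2/n): √(2/36) = 0.236 and √(2/32) = 0.25. Bias divided by standard error shifts the test statistic, which gives the false-positive rate (noncentral t):

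| Loss | n per arm | Bias (SD) | Shift | Type I error |
|---|---|---|---|---|
| 10% | 36 | 0.05 | 0.21 | 5.5% |
| 10% | 36 | 0.10 | 0.42 | 7.0% |
| 20% | 32 | 0.10 | 0.40 | 6.8% |
| 20% | 32 | 0.20 | 0.80 | 12.4% |

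The bias scales in proportion to the assumed difference. At 0.25 SD it would be 0.025 SD with 10% loss and 0.05 SD with 20%. The table describes loss of children from a two-arm comparison such as ALT. It does not measure the effect of discarding questionnaires, because the documents give no rate for that.

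**The case against.** The strongest reply has five parts.

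- **The primary outcome is untouched by the removal rule.** This stands. Forms are discarded, not children, and blood samples are collected separately. A reader might infer that the removal step corrupts the ALT and GGT results; the documents do not support that.
- **Nothing says that the analysis is of completers.** This stands as stated. A reader might infer that the whole trial will be analysed complete-case. That is an inference from the named tests. Paired tests can be run after imputation, and the rule for missing values may sit in an analysis plan that is not shown. A paired test at week 24 would also keep a child lost later. The finding therefore does not rest on a missing imputation rule. It rests on a stated deletion step, and on stated tests that do not by themselves give the protection claimed.
- **Blinding already covers the judgement of validity.** This stands in part. The Blinding section covers data assessors, but the article does not say that the researcher who helps to complete and then checks the forms is one of them. Table 2 includes data collection in the intervention team's training. Neither a blinded nor an unblinded check is established.
- **A 20% planning figure and about 10% expected attrition are compatible.** This stands. Planning for more loss than expected is ordinary caution, so the two figures are not treated as a contradiction.
- **The bias figures depend on one-sided informative dropout.** This stands. A reader might conclude that completers would flatter the intervention. The reasons given for leaving are financial or about time, the Discussion hopes that the intervention improves compliance, and other dropout patterns reverse the sign.

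**Conclusion.** The concern holds in a limited form: the promise in the Discussion ("we will conduct the analysis on an intention-to-treat basis") is not matched by the methods as written. Questionnaire outcomes are exposed to undefined removal after randomisation. ALT and GGT are exposed to loss of children without the chosen follow-up value, unless values are imputed.

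If loss is informative in one arm only and dropouts are 0.5 to 1.0 SD worse, a nominal 5% test would run at about 5.5 to 7% with the attrition the Discussion expects, and at about 7 to 12% with the loss the sample size allows for. These are illustrations under assumption, not predictions. The size for questionnaire outcomes cannot be computed from the documents. The plan should be changed, because the remedy is cheap and uses visits already scheduled.

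**What to change.** In Statistical analyses:

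1. State that all randomised children are analysed in the arm to which they were allocated.
2. Replace the elimination step, here and in Data collection and management. Keep every returned questionnaire and handle missing items by the instrument's own scoring rule. Define any validity check in advance and have it done by the blinded personnel of the Blinding section.
3. For continuous outcomes, replace the paired tests with a likelihood-based mixed model that compares the arms over baseline and the five scheduled visits. Children with partial follow-up then contribute. The model also gives a comparison between arms, which a paired test within an arm does not.
4. Add one sensitivity analysis for informative dropout, for example delta-adjusted or reference-based.

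Optionally, say that 20% is a cautious planning figure and about 10% the expected attrition.

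The cost is a change of wording and slightly more analysis work. No new data, visits or children are needed. The mixed model assumes that missingness is explained by the observed data, which is why the sensitivity analysis is needed.

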### Outcome

The primary outcome are serum biomarkers such as alanine aminotransferase (ALT) and gamma-glutamyl transferase (GGT). Second outcomes are: aspartate aminotransferase, and liver imaging (liver ultrasound and magnetic resonance imaging), BMI, waist-to-hip ratio and quality of life. In addition, socio-demographic characteristics such as age, gender, and ethnicity will be recorded. All outcomes were measured at baseline, week 4, week 16, week 24, week 36, and week 48 to determine the trajectory of change in outcome variables over intervention process.

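### Hepatic steatosis is named inconsistently, and no between-arm test is tied to quantitative liver fat

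*Protocol article*

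**What the plan says.** **Outcome section.** The secondary outcomes include "liver imaging (liver ultrasound and magnetic resonance imaging"). No quantity, cut-off or order of priority between the two modalities is given. All outcomes are scheduled for baseline and weeks 4, 16, 24, 36 and 48. The Abstract lists the same imaging among the primary outcomes.

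**Data collection and management.** "1H-MRS were taken to determine hepatic steatosis". Neither outcome list names 1H-MRS, and this section gives no schedule for it.

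**Statistical analyses.** The intervention's effect on NAFLD is to be "analyzed using McNemar's test for paired categorical data and χ^2^ or Fisher's exact test for independent categorical data, as appropriate". Changes in continuous variables get a paired t-test. A t-test and ANOVA are also named for inference, without an outcome. Liver fat content appears once, in an analysis of covariance that "evaluated whether baseline variables predicted changes in liver fat content and ALT during 6 months of treatment".

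**Eligibility criteria.** The only NAFLD criteria in the document are those for entry. They accept any liver imaging technique or biopsy, and they also require ALT above 1.5 times the upper limit (60 U/L) for more than 3 months.

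**The concern.** The trial is about treating NAFLD, so liver fat is close to its central question. Two things are left open.

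- **Who counts as improved.** NAFLD yes/no is in neither outcome list and has no follow-up rule. It could come from ultrasound, from an MR reading or from the entry criteria. If the entry criteria were reused, a child could stop being a case through a fall in ALT alone, with liver fat unchanged.
- **How the arms are compared on liver fat.** A substantial fall that stops short of the cut-off counts as no change in a yes/no analysis. The continuous measurement would capture it, but no treatment comparison is assigned to that measurement.

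If modality, cut-off and test are chosen after the data are seen, the result on liver fat will carry little weight.

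**Working it through.** **Step 1. What each named analysis answers**

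| Analysis in the plan | Compares arms? | Tied to quantitative liver fat? |
|---|---|---|
| McNemar on NAFLD | No, within group | No |
| Chi-square or Fisher on NAFLD | Yes, if the independent groups are the arms | No, yes/no |
| Paired t-test on continuous changes | No, within group | Only by implication |
| ANCOVA | Asks about baseline predictors | Yes, but not as a treatment comparison |
| t-test, ANOVA | Possibly | No outcome named |

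**Step 2. McNemar's test here.** Every child is enrolled with NAFLD. If baseline status is the entry diagnosis, no child can move from no to yes, so one discordant cell is zero by design. With k children losing the diagnosis, the exact two-sided p-value is 2 × 0.5^k: 0.0625 for k = 5 and 0.031 for k = 6. Six children in one arm (6/32 = 19%) give significance, whatever happens in the other arm.

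**Step 3. The plan's sample size.** The inputs, from the Sample size section, are "Effect size) was estimated to be −1.35" (for ALT), "The sample size required will be 32 study subjects per group by power analysis in reaching 80% effectiveness", a two-sided 5% level, and "Based on a 20% failure rate, this part of the study required 80 subjects, 40 in each group".

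- Inflation: 32/(1 − 0.20) = 40. This reproduces.
- n per group = 2(1.960 + 0.842)²/1.35² = 8.6, so 9 (10 by the t formula). The stated 32 does not reproduce.
- Worked backwards, 32 per group at 80% power corresponds to d = √(2 × 7.85/32) = 0.70 (0.711 by the t formula).

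That mismatch is a separate matter. It matters here only because neither 0.71 nor 1.35 can be taken as the expected liver-fat effect, so a range of d is shown.

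**Step 4. Power, continuous against yes/no.** Assumptions: liver fat is normal on the analysis scale, the arms differ by d SD, and a proportion p₀ of controls falls below the cut-off. The intervention proportion is then p₁ = Φ(Φ⁻¹(p₀) + d). For d = 0.711, the p₀ values 5, 10, 20, 30 and 50% give p₁ = 17.5, 28.4, 44.8, 57.4 and 76.1%. Chi-square (uncorrected) and Fisher power come from full enumeration of both binomials, with 32 per arm and two-sided 0.05.

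Cells show power (%) as chi-square / Fisher:

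| d | t-test | p₀ 5% | 10% | 20% | 30% | 50% |
|---|---|---|---|---|---|---|
| 0.5 | 50.4 | 19.5 / 5.8 | 25.3 / 14.8 | 32.0 / 23.6 | 36.2 / 27.0 | 36.5 / 27.3 |
| 0.711 | 79.9 | 38.1 / 18.5 | 47.6 / 35.4 | 57.9 / 47.9 | 63.4 / 53.4 | 60.3 / 50.2 |
| 1.0 | 97.6 | 69.3 / 52.4 | 80.3 / 71.7 | 87.6 / 81.4 | 89.9 / 84.5 | 85.4 / 78.8 |
| 1.35 | 100.0 | 94.3 / 89.6 | 97.8 / 95.9 | 99.0 / 98.0 | 99.0 / 98.1 | 97.4 / 95.3 |

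Smallest and largest loss in each row:

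- d = 0.5: 50.4 − 36.5 = 14 points to 50.4 − 5.8 = 45 points
- d = 0.711: 79.9 − 63.4 = 17 to 79.9 − 18.5 = 61
- d = 1.0: 97.6 − 89.9 = 8 to 97.6 − 52.4 = 45
- d = 1.35: 100.0 − 99.0 = 1 to 100.0 − 89.6 = 10

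**Step 5. Baseline adjustment.** With an assumed baseline to follow-up correlation r, the effective d is d/√(1 − r²). For d = 0.711 this is 0.82 at r = 0.5 and 0.89 at r = 0.6, which raises power from 80% to about 90% and 94%.

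**The case against.** **The names may be loose and not contradictory.** The Outcome and Data collection sections name modalities, not definitions, and 1H-MRS is an MR method that may be the MRI meant in the outcome list. This stands: a reader might infer three conflicting definitions of steatosis, and the text does not show that. Ultrasound is still unranked beside the MR reading, however, and the yes/no rule has no stated source.

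**The quantitative data are not thrown away.** A reader might infer that the plan discards liver fat. It does not: t-test and ANOVA are named, continuous changes get a paired t-test, and the ANCOVA uses liver fat content. The clause on categorical tests does not say that a continuous reading will be cut. What remains is that none of this is tied to a between-arm comparison of liver fat.

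**The power loss depends on chosen inputs.** This also stands. At the only effect size in the document (1.35, for ALT) the loss is small. The largest losses need Fisher's test with 5% control responders. By the usual rule of expected counts of at least 5, chi-square would apply at 10% or more, and at 0.71 SD the loss is then 17 to 32 points.

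**Imaging is secondary, and an article condenses.** The Outcome section does make imaging secondary, and nothing makes yes/no NAFLD the headline result. Cut-offs and modality ranking could sit in a fuller document. The article does, however, state the outcomes, the measurement and the tests, and they do not line up.

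**Conclusion.** The point holds as an inconsistency in naming plus a missing link between liver fat and a treatment comparison. Both follow from the text and need no power assumption.

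The size is conditional. At 32 per arm with 5% to 50% control responders, the loss runs from about 1 point (1.35 SD) to about 61 points (0.71 SD with Fisher's test). The inputs are a normal model, an assumed effect and an assumed responder rate. A reader might infer that a real fall in liver fat would probably be missed. The figures do not support that in general: at 0.71 SD chi-square power exceeds 50% in three of the five scenarios, and at 1.35 SD it is at least 94% in all five. The zero cell in McNemar's test assumes that baseline status is the entry diagnosis.

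This should be changed, but it does not threaten the primary outcomes listed in the Outcome section.

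**What to change.** 1. Name one quantity in the Abstract, Outcome, Data collection and Statistical analyses sections: liver fat content measured by 1H-MRS. State whether this is the MRI of the outcome list, and describe ultrasound as supportive.
2. Compare liver fat between arms as a continuous outcome by ANCOVA with treatment group and baseline liver fat as terms, on the log scale if skewed.
3. State one time point at which it is already measured, reconciling the week 48 schedule in Outcome with the 6 months in Statistical analyses.
4. If a yes/no NAFLD result is kept, define it from the same reading with one pre-stated cut-off, compare it between arms and label it supportive. Do not use McNemar's test as evidence of a treatment effect.

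**Cost.** The change is to wording, provided 1H-MRS is the MR examination already scheduled in the Outcome section. The Data collection section gives no 1H-MRS dates, so the sponsor should confirm this. If it is a different examination, choose a time point at which 1H-MRS is already done. The small downside is that the yes/no result becomes supportive.
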